## 6.1 Sample Size, Dose Levels and Justification of the Dose

The sample size will be 20 for this pilot trial.

This study will use the maximum tolerated dose (MTD) established in the study conducted by Pardee and colleagues (CCCWFU 29109; IRB00012124). This MTD for single-agent use of CPI-613 infused over 2 hours is 3,000 mg/m^2^.

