# 9.0 STATISTICAL CONSIDERATIONS

This is a pilot study with the primary goal to be able to determine initial estimates of response rate (RR), and secondary goals to determine progression-free survival (PFS) and overall survival (OS). Data from this trial will also provide additional data concerning the safety profile of the CPI-613 therapy. We now describe anticipated accrual rates, proposed analyses, and sample size considerations.

Accrual Rate

We anticipate accruing one to two patients per month for this protocol. Thus, we anticipate that we will reach the target sample size of 20 patients treated at MTD within eighteen months.

Proposed Analyses

The analyses for this protocol will be primarily descriptive. With a sample size of 20 treated at MTD, we will be able to get initial estimates of RR, PFS, OS, and safety and toxicity.

For the primary outcome of tumor response rate we will present the proportion of patients who are CR, PR, SD or PD (Complete response, Partial response, stable disease and progressive disease, respectively). In addition, we will estimate the proportion of responders as the percent of patients who are SD, PR and CR, as well as RR (sum of PR + CR) and Disease Control Rate (DCR, which is the sum of SD, PR and CR). For these rates we will also include 95% confidence intervals.

For the time-to-event outcomes, we will estimate survival curves for OS and PFS using Kaplan-Meier techniques. In addition, we will estimate the 6 month and 1-year OS and PFS rates for these participants. We will estimate median overall and progression free survivals for these patients as well. We will also examine safety and toxicities for these 20 patients by looking at each toxicity identified earlier in the protocol by grade.

Sample Size Considerations

Since this is a single arm pilot study, our primary goal is to gather preliminary data on response rates and not to test a specific hypothesis per se. With this sample size we will be able to estimate the response rate using a 2-sided 95% confidence interval with an interval that will extend no more than 0.21 from the observed response rate (if we conservatively assume a response rate of 0.5 for calculations).

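### The stated precision is wrong: with 20 patients the 95% interval reaches 0.219 (normal) or 0.228 (exact) from a 50% response rate, not at most 0.21

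*Protocol*

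**What the plan says.** Section 6.1 of the Protocol fixes the size of the trial: "The sample size will be 20 for this pilot trial". Section 9.0 repeats the figure under Accrual Rate and, under Sample Size Considerations, explains that "our primary goal is to gather preliminary data on response rates and not to test a specific hypothesis per se". It then states the precision that 20 patients will deliver for the two-sided 95% interval on that rate: "with an interval that will extend no more than 0.21 from the observed response rate". The condition attached is "if we conservatively assume a response rate of 0.5 for calculations".

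Under Proposed Analyses, after listing the response rate (RR) and the disease control rate (DCR), the section adds "For these rates we will also include 95% confidence intervals". No interval method is named there or elsewhere in the protocol. No other precision figure is given, and there is no hypothesis test, power calculation or decision threshold.

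**The concern.** The sentence gives an upper bound, so a value even slightly above 0.21 makes it false. The familiar normal-approximation formula at 20 patients and a rate of 0.5 gives a value nearer 0.22, which suggests that 0.219 was truncated instead of rounded up.

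Two things are at stake. First, this is the only numerical property that the protocol claims for its sample size, and readers judging whether 20 patients are enough are told that the estimate will be tighter than it will be. Second, treating 0.5 as the conservative case points to the normal approximation, because that interval is widest at 0.5. If the same interval were carried into the primary analysis, it would perform poorly when few patients respond. With no responders among 20 it collapses to 0% to 0%.

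**Working it through.** **Inputs**

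- n = 20 (Sections 6.1 and 9.0)
- two-sided 95% interval, so z = 1.96 (Section 9.0)
- assumed response rate p = 0.5 (Section 9.0)
- claimed maximum distance from the observed rate: 0.21 (Section 9.0)
- interval method: not named

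**Step 1. Try to reproduce the stated figure**

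Normal half-width = z × √(p(1 − p)/n) = 1.96 × √(0.25/20) = 1.96 × 0.1118 = 0.219.

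The interval is 0.281 to 0.719. The result rounds to 0.22, and 0.21 is not reproduced.

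The sample size at which this formula meets 0.21 is n = 0.25 × (1.96/0.21)² = 21.8, so 22 patients (half-width 0.209). With 21 patients it is still 0.214.

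**Step 2. Exact interval at the same point**

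Clopper-Pearson for 10/20: 0.272 to 0.728, half-width 0.228. With this interval, 24 patients bring the half-width at p = 0.5 to 0.209 (12/24).

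**Step 3. Could another method rescue the sentence?**

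Because no method is named, the distance from the observed rate to the further confidence limit was computed for every count from 0 to 20. Results are symmetric about 10, so a maximum at 6/20 also occurs at 14/20.

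| Method | Distance at 10/20 | Largest distance | Count (up to 10) at the maximum | Counts above 0.21 |
|---|---|---|---|---|
| Normal | 0.219 | 0.219 | 10 | 8–12 |
| Exact | 0.228 | 0.243 | 6 | 2–18 |
| Wilson | 0.201 | 0.219 | 6 | 3–8, 12–17 |
| Agresti-Coull | 0.201 | 0.222 | 5 | 2–8, 12–18 |
| Jeffreys | 0.207 | 0.218 | 7 | 5–9, 11–15 |

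Wilson, Agresti-Coull and Jeffreys meet 0.21 at exactly 10/20. For these three, however, 0.5 is not the least favourable case, and each exceeds 0.21 at other counts. The same is true of the exact interval, whose worst case is 6/20 (0.119 to 0.543; 0.543 − 0.300 = 0.243). As a bound on the distance from the observed rate, 0.21 fails for all five.

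**Step 4. If the normal interval were used for the result**

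The protocol gives no expected response rate for CPI-613. The low rates below are assumptions, shown as a range. Coverage is the sum of the binomial(20, p) probabilities over the counts whose interval contains p.

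| Assumed true rate | Normal coverage | Exact coverage |
|---|---|---|
| 5% | 64% | 98.4% |
| 10% | 88% | 98.9% |
| 15% | 82% | 97.8% |

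At 5%, most of the shortfall comes from one outcome. The chance of no responders is 0.95²⁰ = 36%, and the normal interval for 0/20 is 0% to 0%, which excludes 5%. The exact interval for 0/20 is 0% to 16.8%. For 1, 2 or 3 responders the normal lower limit is negative (for 2/20, 0.100 − 0.131 = −0.031), whereas the exact interval for 2/20 is 1.2% to 31.7%.

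**The case against.** The strongest reply is that the error is trivial. It is under 0.01 with the normal interval and under 0.02 with the exact one at p = 0.5. The trial is a descriptive pilot without a hypothesis, and no go/no-go rule uses the figure. The protocol also does not derive 20 from 0.21. It takes 20 as given and reports the precision that follows, so the 22 patients in Step 1 measure the size of the error and do not call for a larger trial. All of this stands, and it limits the weight of the point.

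A second reply is that three respectable intervals do satisfy 0.21 at exactly 0.5, the rate the sentence assumes. That is true at that one point. But the sentence presents 0.5 as the conservative case for a bound on the distance from whatever rate is observed, and for those intervals other outcomes are worse.

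A third reply is that the coverage argument depends on a choice the protocol has not made. A normal-approximation planning figure does not commit the analysis to that interval, the method is commonly left to a statistical analysis plan, and the low response rates are assumed. This also stands. Step 4 is a conditional warning and a reason to name the method while the sentence is being corrected. The absence of a named method is not itself the error. The wrong number is printed in the protocol, and nothing elsewhere in the protocol corrects it.

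**Conclusion.** The concern holds. At 20 patients and a response rate of 0.5, the 95% interval extends 0.219 (normal) or 0.228 (exact) from the observed rate, so the stated maximum of 0.21 is wrong under both. Across all possible outcomes the bound also fails for Wilson, Agresti-Coull and Jeffreys. This conclusion uses only inputs stated in the protocol.

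The practical size is modest: 0.01 to 0.02 at p = 0.5, equivalent to 2 patients (normal) or 4 patients (exact), and up to 0.033 (0.243 − 0.21) at the exact interval's worst case. The design remains sound and 20 patients can stay. The sentence should still be corrected, because it is the only quantitative rationale for the sample size and it describes the primary endpoint. The further risk, an interval that is too narrow when few patients respond, arises only if the normal interval is used for the result and the true rate is low.

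**What to change.** Keep 20 patients and replace the precision sentence in Section 9.0, Sample Size Considerations, with wording such as:

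> With 20 patients, the exact (Clopper-Pearson) two-sided 95% confidence interval for the response rate has limits no more than 0.25 from the observed rate; for example, 10/20 gives 27.2% to 72.8%, 2/20 gives 1.2% to 31.7%, and 0/20 gives 0% to 16.8%.

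Under Proposed Analyses, name the same exact interval for RR and DCR, so that the planning figure and the reported result match and can be checked.

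The least that would make the stated calculation correct is to change 0.21 to 0.22 and identify it as the normal approximation. The exact wording is better because it holds for every possible outcome and remains informative when there are few or no responders.

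The cost is one sentence of wording plus the name of the method, and a stated precision that looks slightly less favourable. Sample size, conduct and data collection do not change.

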# 10.0 Data Management

| Informed consent document | At time of registration | ORIS |
| --- | --- | --- |
| Protocol registration form | At time of registration | ORIS |
| Efficacy assessment form (Appendix D) | Within 1 week | REDCap |
| Phone follow-up form (Appendix E) | Within 1 week | REDCap |
| Withdrawal of participation form (Appendix F) | Within 1 week | REDCap |
| Tumor measurement form (Appendix G) | Within 1 week | REDCap |

# APPENDIX A – REGISTRATION GUIDELINES AND FORMS

The following guidelines have been developed in order to ensure timely registration of your patient.

All patients entered on any CCCWFU trial, whether treatment, companion, or cancer control trial, **must** be registered with the CCCWFU Protocol Registrar or entered into ORIS Screening Log within 24 hours of Informed Consent. Patients **must** be registered prior to the initiation of treatment.

In order to ensure prompt registration of your patient, please:

1. Complete the Eligibility Checklist (attached)
2. Complete the Protocol Registration Form (attached)
3. Alert the WFUHS registrar by phone, *and then* send the signed Informed Consent Form, Eligibility Checklist and Protocol Registration Form to the registrar, either by fax or

e-mail.

Contact Information:

Protocol Registrar [contact]

Protocol Registrar [contact]

Protocol Registrar E-MAIL ([[contact]](mailto:[contact]))

*Protocol Registration is open from 8:30 AM - 4:00 PM, Monday-Friday.

1. Please fax/e-mail ALL eligibility source documents with registration. Patients **will not** be registered without all required supporting documents.

**Note:** If labs were performed at an outside institution, please provide a printout of the results. Please ensure that the most recent lab values are sent.

| **CCCWFU # Eligibility Checklist** | | | | |
| --- | --- | --- | --- | --- |
| **Yes** | **No** | **N/A** | Inclusion Criteria (All responses must be **YES** in order to enter study) | **Eligibility Confirmation (registrar)** |
| 🞎 | 🞎 | 🞎 | 1. Does the patient have histologically or cytologically proven extensive stage SCLC that has relapsed or been refractory after at least one line of chemotherapy. |  |
| 🞎 | 🞎 | 🞎 | 1. Does the patient have an ECOG performance status of < 2? |  |
| 🞎 | 🞎 | 🞎 | 1. Is the patient 18 years of age or older? |  |
| 🞎 | 🞎 | 🞎 | 1. Does the patient have an estimated survival of > 1 month? |  |
| 🞎 | 🞎 | 🞎 | 1. Is the patient free from acute toxic effects from previous treatment superior to grade 1 at the start of treatment with CPI-613? |  |
| 🞎 | 🞎 | 🞎 | 1. If the patient is a woman of child-bearing potential (i.e., pre-menopausal or not surgically sterile), does she agree to use accepted contraceptive methods (abstinence, intrauterine device [IUD], oral contraceptive or double barrier device) during the study, and agree to have a negative serum or urine pregnancy test within 1 week prior to treatment initiation? |  |
| 🞎 | 🞎 | 🞎 | 1. If the patient is a fertile man, does he agree to practice effective contraceptive methods during the study, unless documentation of infertility exists? |  |
| 🞎 | 🞎 | 🞎 | 1. Does the patient have documentation of the following laboratory values?  - platelet count ≥100,000 cells/mm^3^ or ≥100 bil/L - absolute neutrophil count [ANC] ≥1,500 cells/mm^3^ or ≥1.5 bil/L - aspartate aminotransferase [AST/SGOT] ≤3x upper normal limit [UNL] - bilirubin ≤1.5x UNL - serum creatinine ≤1.5 mg/dL or 133 µmol/L - Albumin >3.0 g/dL or >30 g/L. |  |
| 🞎 | 🞎 | 🞎 | 1. Is the patient mentally competent, able to understand and willing to sign an IRB-approved written informed consent document? |  |
| 🞎 | 🞎 | 🞎 | 1. Does the patient have access via a double lumen central line (e.g., portacath)? |  |
|  | | | | |
| **Yes** | **No** | **N/A** | Exclusion Criteria (All responses must be **NO** in order to enter study) | **Eligibility Confirmation (registrar)** |
| 🞎 | 🞎 | 🞎 | 1. Is the patient receiving any other standard or investigational treatment for their cancer, or have they received any other investigational agent for any indication within the past 2 weeks prior to initiation of CPI-613 treatment? |  |
| 🞎 | 🞎 | 🞎 | 1. Does the patient have a serious medical illness that would potentially increase his or her risk for toxicity? |  |
|  |  |  | 1. Does the patient have any active uncontrolled bleeding or bleeding diathesis? |  |
| 🞎 | 🞎 | 🞎 | 1. Is the patient a pregnant woman, or a woman of child-bearing potential who is not using reliable means of contraception? |  |
| 🞎 | 🞎 | 🞎 | 1. Is the patient a lactating female? |  |
| 🞎 | 🞎 | 🞎 | 1. Is the patient a fertile man who is unwilling to practice contraceptive methods during the study period? |  |
| 🞎 | 🞎 | 🞎 | 1. Is the patient’s life expectancy less than 1 month? |  |
| 🞎 | 🞎 | 🞎 | 1. Has the patient received treatment with any anti-cancer therapy within the 2 weeks prior to treatment with CPI-613? |  |
| 🞎 | 🞎 | 🞎 | 1. Does the patient have an unrelated central nervous system (CNS) or epidural tumor? |  |
| 🞎 | 🞎 | 🞎 | 1. Does the patient have any condition or abnormality which may, in the opinion of the investigator, compromise his or her safety? |  |
| 🞎 | 🞎 | 🞎 | 1. Is the patient unwilling or unable to follow protocol requirements? |  |
| 🞎 | 🞎 | 🞎 | 1. Does the patient have active heart disease including myocardial infarction within previous 6 months, symptomatic coronary artery disease, arrhythmias not controlled with medication, or symptomatic congestive heart failure? |  |
| 🞎 | 🞎 | 🞎 | 1. Does the patient have evidence of active infection, or serious infection (e.g septic shock with multi-organ dysfunction) within the past month? |  |
| 🞎 | 🞎 | 🞎 | 1. Does the patient have known HIV infection? |  |
| 🞎 | 🞎 | 🞎 | 1. Does the patient require immediate palliative treatment of any kind, including surgery? |  |

Signature: ___________________________________ Date: _________________

*Please send source documentation with Eligibility Form.*

**CCCWFU # 62113 Protocol Registration Form**

| **DEMOGRAPHICS** | | | | |
| --- | --- | --- | --- | --- |
| Patient: Last Name: _____________________ | | | First Name: ____________________________ | |
| MRN: ___ ___ ___ ___ ___ ___ ___ ___ | | | DOB (mm/dd/yy): ___ ___ / ___ ___ / ___ ___ | |
| SEX: | 🞎 Male  🞎 Female | | Ethnicity (choose one): | 🞎 Hispanic  🞎Non-Hispanic |
| Race (choose all that apply): | | 🞎 WHITE 🞎BLACK 🞎 ASIAN  🞎 PAIFIC ISLANDER 🞎 NATIVE AMERICAN | | |
| Height: ___ ___**.**___ inches | | | Weight: ___ ___ ___**.**___lbs.(actual) | |
| Surface Area: ___ ___**.**___m^2^ | | |  | |
| Zip Code: ___ ___ ___ ___ ___  Primary Diagnosis: _____________________________________________________________ | | | | |
| Date of Diagnosis: ___ ___ /___ ___/___ ___ | | |  | |

ECOG performance status: __________________________________

Prior Treatments for Lung Cancer:

Name Duration

________________________________ ___________________________________

________________________________ ___________________________________

________________________________ ___________________________________

________________________________ ___________________________________

________________________________ ___________________________________

________________________________ ___________________________________

| **PROTOCOL INFORMATION** | |
| --- | --- |
| Date of Registration: | ___ ___ / ___ ___ / ___ ___ |
| MD Name (last) : | ______________________ |
| Date protocol treatment started: | ___ ___ / ___ ___ / ___ ___ |
| Informed written consent:  (consent must be signed prior to registration) | 🞎 YES 🞎 NO |
| Date Consent Signed: | ___ ___ / ___ ___ / ___ ___ |
| PID # (to be assigned by ORIS): | ___ ___ ___ ___ ___ ___ ___ ___ |

*Protocol Registrar can be contact by calling [contact] between 8:30 AM and 4:00 PM, Monday – Friday.*

*Completed Eligibility Checklist and Protocol Registration Form must be hand delivered, faxed or e-mailed to the registrar at [name] or* [*[contact]*](mailto:[contact])*.*

**CCCWFU # 62113 Eligibility Source Documentation Checklist**

**(to be submitted with Protocol Registration Form)**

| **Source Documents Needed (see eligibility form above for changes)** | | | **✓ or N/A** | |
| --- | --- | --- | --- | --- |
|  | Pathology report confirming histologically or cytologically proven extensive stage SCLC that has relapsed or been refractory after one line of chemotherapy? |  | |  |
|  | Lab report documenting all initial required lab values |  | |  |
|  | Documentation that the patient is free from acute toxic effects from previous treatment superior to grade 1 |  | |  |
|  | Documentation of ECOG performance status of 0, 1, or 2 |  | |  |
|  | Documentation of expected survival > 1 month |  | |  |
|  | Most recent H&P documenting patient is 18 years of age or older |  | |  |
|  | For female patients of child-bearing potential (i.e., pre-menopausal or not surgically sterile), documentation that the patient agrees to use accepted contraceptive methods (abstinence, intrauterine device [IUD], oral contraceptive or double barrier device) during the study, and agrees to have a negative serum or urine pregnancy test within 1 week prior to treatment initiation. |  | |  |
|  | For male patients, documentation of infertility OR for fertile men, documentation that patient agrees to practice effective contraceptive methods during the study |  | |  |
|  | Lab report performed (< 2 weeks) documenting the following values:   - Platelet count ≥100,000 cells/mm^3^ or ≥100 bil/L - Absolute neutrophil count ≥1500 cells/mm^3^ or ≥1.5 bil/L - Aspartate aminotransferase [AST/SGOT] ≤3x upper normal limit [UNL] - Bilirubin ≤1.5x UNL - Serum creatinine ≤1.5 mg/dL or 133 µmol/L - Albumin > 3.0g/dL or 30 g/L |  | |  |
|  | Documentation that the patient is mentally competent, able to understand and willing to sign an IRB-approved written informed consent document |  | |  |
|  | Copy of signed consent form |  | |  |
|  | Documentation that the patient is not receiving any other standard or investigational treatment for their cancer, or has received any other investigational agent for any indication within the past 2 weeks prior to initiation of CPI-613 treatment |  | |  |
|  | Documentation that the patient has not received cancer immunotherapy within the past 2 weeks prior to initiation of CPI-613 treatment |  | |  |
|  | Documentation that the patient does not have a serious medical illness that would potentially increase his or her risk for toxicity |  | |  |
|  | Documentation that the patient does not have any active uncontrolled bleeding or bleeding diathesis |  | |  |
|  | Documentation that the patient does not have an unrelated central nervous system (CNS) or epidural tumor |  | |  |
|  | Documentation that the patient is free of any condition or abnormality which may, in the opinion of the investigator, compromise his or her safety |  | |  |
|  | Documentation that the patient does not have active heart disease (including myocardial infarction within previous 6 months, symptomatic coronary artery disease, arrhythmias not controlled with medication, or symptomatic congestive heart failure) |  | |  |
|  | Documentation that the patient does not have a history of additional risk factors for torsade de pointes (e.g., heart failure, hypokalemia, family history of Long QT Syndrome) |  | |  |
|  | Documentation that the patient does not have evidence of active infection, or serious infection (e.g septic shock with multi-organ dysfunction) within the past month |  | |  |
|  | Documentation that the patient does not have known HIV infection |  | |  |
|  | Documentation that the patient does not require immediate palliative treatment of any kind, including surgery |  | |  |

# APPENDIX B STRC SAE REPORTING GUIDELINES

**Mandatory Safety and Toxicity Review Committee (STRC; Previously CROC)**

**Serious Adverse Event (SAE) Notification Procedure**

**Mandatory STRC SAE Reporting Requirements – Revised 6/05/2012**

This document describes STRC reporting and use of the electronic submission form that is submitted **for unexpected grade 4 and any grade 5 (death during protocol intervention) SAEs on CCCWFU Institutional interventional trial patients**. There are multiple entities that require reporting of SAEs. Each entity has different rules for what is reported, and how it is reported.

Rules used by other entities (Institutional Review Board (IRB), AdEERS, MedWatch, etc.) should NOT be used to evaluate whether an event should be reported to STRC. Only the rules for reporting described in this document should be considered.

As defined in the NCI summary IV reporting guidelines, **CCCWFU Institutional studies covered by these reporting requirements are defined as: In-house, internally reviewed trials, including those collaborative studies conducted with industry sponsorship in which the center is a primary contributor to the design, implementation, and monitoring of the trial, or participation in a multi-site trial initiated by an institutional investigator at another center.** Institutional trials are almost always authored by a researcher here at CCCWFU. Institutional protocols are labeled NCI Code=”I” for Institutional on the protocol screen in ORIS. Cooperative group protocols are **not** considered Institutional, but Research Base trials **are** classified as Institutional.

The STRC is responsible for reviewing SAEs for CCCWFU Institutional studies, as defined above. STRC currently requires that unexpected grade 4 and all grade 5 SAEs on these trials be reported to them for review. All Clinical Research Management (CRM) staff members assisting a PI in documenting and reporting an SAE that qualifies for STRC reporting are responsible for informing a clinical member of the STRC by phone, followed by informing the entire committee via the required email notification.

